### Assessment of hepatic steatosis and fibrosis

Hepatic steatosis and fibrosis among all participants will be examined by transient elastography with fibroscan by the same gastroenterologist at the beginning and end of the study. Patients will be asked to lie down on their back and place the right hand above their head. Then the probe will be placed on the right side of the liver in patients’ intercostal area. The results of liver fibrosis will be expressed as Kilopascal (Kpa). The interpretation of fibrosis assessment results will be based on METAVIR Score [31]. The controlled attenuation parameter (CAP) test will be used to assess steatosis and the results will be reported in dB/m. CAP results will vary between 100 and 400 dB/m.

### Biochemical assessment

To assess the level of liver enzymes (ALT, AST, GGT), blood sugar and lipid profiles (including total cholesterol, serum triglyceride and HDL cholesterol), 10 cc of intravenous blood samples will be collected after 10–12 h of fasting. Blood samples are centrifuged for 10 min at 2606.8 G and 4 °C to separate serum samples. The level of ALT and AST enzymes will be determined by photometry (Pars Azmoun) proposed by the IFCC (International Federation of Clinical Chemistry) method. GGT levels will also be assessed using the calorimetric-kinetic method proposed by the IFCC. Fasting blood glucose (FBS) levels will be measured by glucose oxidase and fasting insulin levels will be measured by ELISA method. Serum concentrations of total cholesterol and triglycerides will be measured by laboratory methods using enzymes such as cholesterol esterase, cholesterol oxidase and glycerol phosphate oxidase, respectively, using standard kits. HDL-C will be measured after deposition of apolipoprotein-B, which contains lipoproteins with phosphotungstic acid. LDL-C will be calculated from the values of TC, TG, HDL_C by the formula of Friedwald [32].

### Glucose homeostasis assessment

Homeostatic Model Assessment of Insulin Resistance (HOMA) and Quantitative Insulin Sensitivity Check Index (QUICKI) will be calculated based on suggested formulas [33, 34]

### Blood pressure assessment

Systolic blood pressure (SBP) and diastolic blood pressure (DBP) will be measured after 5 min of rest with a mercury sphygmomanometer from the patient's right hand while sitting. Patients should not drink, exercise or smoke for one hour prior to blood pressure assessment. They must also have an empty bladder before measuring their blood pressure. Blood pressure will be taken twice, 5 min apart, while the patient is at rest. Systolic blood pressure is equivalent to the pressure measured after hearing the first korotkoff sound, and diastolic blood pressure is equivalent to the pressure measured when the korotkoff sound disappears. The mean of the two measurements will be considered as systolic and diastolic blood pressure.

### Anthropometric assessments

To assess height, the person must be standing and barefoot with an accuracy of 0.5 cm. Weight will be measured using a digital scale with a minimum of clothing and barefoot with an accuracy of 100 gr. Waist circumference will be measured using a tape measure in the middle of the distance between the super iliac bone and the last rib with an accuracy of 0.5 cm. BMI will also be obtained by dividing weight in kilograms by height squared in meters [35].

### Other variables assessments

A general questionnaire will be used to collect information about participants’ age, sex, marital status (single /married), education (yes/no), supplement use (yes/ no), medical history, tobacco use (non-smoker /smoking history/smoker), occupation, history of drug use.

### Statistical analysis

In this study, all analyses will be done using SPSS software version 26. Normal distribution of data will be assessed by the application of Kolmogorov–Smirnov test. In case of a non-normal distribution, we will apply logarithmic transformation. Results will be reported as mean ± standard deviations (SD) or medians (interquartile ranges). General characteristics and dietary intake of individuals between the two groups will be compared using independent t-test and chi-square test as needed. Repeated measure analysis of variance (RM-ANOVA) will be used to examine the effects of probiotic yogurt consumption on outcome variables, where we will examine the effects of time, intervention as well as time-group interaction effects. In this analysis, baseline values of outcome variables will be controlled for. We will also perform post hoc tests after ANOVA analysis to examine the variables between study groups. In case of any difference between the two groups in terms of dietary intakes (other than the intervention) and physical activity throughout the study, these differences will be adjusted for in the analysis to reach an independent effect of intervention on study outcomes. Statistical significance will be set to 0.05.

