## Patients and methods

### Participants

This study will be a parallel randomized clinical trial (CRT) that will be conducted in Tehran, Iran, in 2021. The sample size was calculated by considering the type 1 error of 5%, the study power of 80% and the hepatic steatosis levels [30] (based on CAP) as a key variable based on data from previous studies. Considering the mean difference in hepatic steatosis levels of 2 dB/mL between the two groups [12], using the suggested formula for parallel clinical trials, we will need 28 patients in each group. However, by taking a possible drop-out of 20% into account, we will recruit 34 patients in each group based on the study inclusion criteria. Outpatients with NAFLD will be recruited from private clinics in Tehran, Iran. The diagnosis of NAFLD will be done by a gastroenterologist based on examination with a fiberoscan. The study is ethically approved by the Bioethics Committee of Tehran University of Medical Sciences, Tehran, Iran, and is registered in the Iranian Registry of Clinical Trials website (http://www.irct.ir).

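### A normality pretest on the sample, not the plan, decides whether each outcome is log-transformed, so the effect measure is not fixed in advance (minor, cheap to correct)

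*Protocol article*

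**What the plan says.** The rule is in the Statistical analysis section of the protocol article. First, "Normal distribution of data will be assessed by the application of Kolmogorov–Smirnov test". Then, "In case of a non-normal distribution, we will apply logarithmic transformation". The model that follows is a repeated-measures one: "Repeated measure analysis of variance (RM-ANOVA) will be used to examine the effects of probiotic yogurt consumption on outcome variables", with time, group and interaction effects and with baseline values controlled for.

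No outcome is assigned a scale beforehand. The direction of skew plays no part in the rule, and no alternative is given if the log does not help. The only related line allows summaries as mean with SD or as median with interquartile range.

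Two other places bear on CAP. The Participants section takes "the hepatic steatosis levels [30] (based on CAP) as a key variable based on data from previous studies" and sizes the trial on an additive difference: "Considering the mean difference in hepatic steatosis levels of 2 dB/mL between the two groups". The section on assessment of hepatic steatosis and fibrosis gives the measuring range: "CAP results will vary between 100 and 400 dB/m".

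**The concern.** A log analysis estimates a ratio of geometric means; a raw analysis estimates a difference in means. Under the stated rule the choice between them is made by a p-value from the trial's own data, so a reader cannot know before the data arrive which quantity will be reported for a given outcome.

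The rule also does not fit the model it feeds. Repeated-measures ANOVA needs both visits on one scale, but a test applied to the data can pass one visit and fail the other. The analyst would then have to choose after seeing the values.

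Finally, the only remedy works in one direction. A log shortens a right tail and lengthens a left one. That suits outcomes that tend to be right-skewed, but not a variable pressed against an upper limit.

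At stake are a predictable effect measure and a small amount of power, not the validity of the test.

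**Working it through.** **Inputs from the article.** 28 evaluable per group (56 in all), 34 recruited per group (68 in all), significance level 0.05, CAP range 100–400 dB/m, CAP difference of 2 units.

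**Assumptions, because the article gives no figures.** Pretest threshold 0.05. Log-normal outcomes with log-SD 0.3–0.8, baseline–end correlation 0.6, 28 per group, and an effect giving about 78% power on the log scale. Two versions of the test, since none is named: plain Kolmogorov–Smirnov with the estimated mean and SD inserted, and the version with Lilliefors critical values.

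**The plan's own figure.** Two-sided, n = 2 × [(1.960 + 0.842) × SD / 2]². Setting n = 28 gives SD = 2 / (2.802 × √(2/28)) = 2.67. The article states no SD, so 28 cannot be reproduced independently. It matters here only because the planned CAP effect is a raw difference.

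**Step 1: how often the log is triggered.** Share of simulated samples of 56 to 68 patients from one log-normal distribution that are logged, Lilliefors version:
- log-SD 0.3: 35–38%
- log-SD 0.5: 74–79%

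With plain Kolmogorov–Smirnov the share at log-SD 0.3–0.5 is only about 2–17%. The same population therefore yields a difference in some trials and a ratio in others, and the split depends heavily on the unstated version of the test.

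**Step 2: disagreement between visits.** If the two verdicts were independent with the same probability p of being flagged, they would disagree with probability 2p(1 − p):
- p = 0.02: 2 × 0.02 × 0.98 = 4%
- p = 0.36: 2 × 0.36 × 0.64 = 46%
- p = 0.75: 2 × 0.75 × 0.25 = 38%

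Simulation with correlation 0.6 gives about 3–45% across log-SDs and test versions, in line with this.

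**Step 3: power.** 1,500 runs per setting, ANCOVA, week-12 verdict governing, Lilliefors version:

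| log-SD | always log | pretest rule | loss (points) |
|---|---|---|---|
| 0.3 | 79.7% | 78.6% | 1.1 |
| 0.4 | 77.1% | 75.6% | 1.5 |
| 0.5 | 79.2% | 78.1% | 1.1 |
| 0.65 | 77.3% | 76.7% | 0.6 |
| 0.8 | 78.1% | 78.1% | 0.0 |

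With plain Kolmogorov–Smirnov the loss is about 2–7 points.

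**Step 4: type I error.** Under no effect the pretest rule rejects in 4.3–5.8% of trials across log-SD 0.3–0.8, for both versions. The simulation standard error is √(0.05 × 0.95 / 1,500) = 0.56 points, so 5 ± 1.96 × 0.56 gives 3.9–6.1%. The observed rates are nominal.

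**Step 5: CAP under assumed shapes.**
- Normal, mean 290–330, SD 40–50, capped at 400: skewness −0.02 to −0.34 raw and −0.46 to −0.74 after the log. The test fires in about 4–7% of samples per visit (either visit: 6–11% of trials). Power under the rule is within 0.2 points of always-raw, and even always-log costs at most 1.6 points.
- Normal, mean 340, SD 50, capped at 400: logged in 16–17%.
- Strongly left-skewed (scaled beta on 100–400): logged in 33–46%. Among logged samples skewness goes from about −0.8 to −1.15, and normality is still rejected in 99–100%.
- Normal, mean 280, SD 40, truncated below at an assumed entry cut of 240: logged in 19–20%, with skewness moving from about +0.67 to +0.47, so here the log helps.

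**The case against.** The strongest reply is that the rule does little harm. It is mechanical and does not look at the treatment effect, so it cannot favour a result, and Step 4 confirms that error rates are not inflated. With the corrected test the power loss is negligible. All of this stands, and it is why the point is minor.

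A second reply is that the threshold, the visit that governs, and whether raw values or residuals are tested may be settled in a fuller document. That also stands: the article says only that data are tested, and these details are not faults in themselves. It does not remove the point, because the article does commit to a sample-driven choice of scale, and nothing elsewhere in it overrides that.

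Three stronger readings are tempting and not supported:
- **That the log will distort CAP, the sizing variable.** The article gives a measuring range but no mean, SD or shape. Under a moderate capped distribution the test seldom fires and power barely moves; it fires more often only if CAP is markedly left-skewed. A lower entry cut would make the log beneficial.
- **That power falls to 62%.** That is raw-scale ANCOVA at log-SD 0.8 regardless of the test. The stated rule would log about 98% of such samples with Lilliefors values, and even plain Kolmogorov–Smirnov leaves power at 75–77%.
- **That the test has too little power to catch skewed enzymes.** This is true of the plain version only.

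**Conclusion.** The point holds as a minor one. The article lets a normality test on the sample choose between a difference and a ratio, offers the log as the only remedy, and can give two verdicts for one outcome that must be modelled on one scale (about 3–45% of simulated trials). The cost is mainly an effect measure unknown in advance, plus about 0–1.5 points of power with the corrected test or 2–7 with the plain one. Type I error is unaffected.

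These sizes rest on log-normal outcomes, correlation 0.6, 28 per group and a 0.05 pretest threshold, none of the distributional inputs being in the article. For right-skewed outcomes the log itself is reasonable; the weakness is leaving the choice to the data. For CAP, the firmest argument is that the sample size is stated as a raw mean difference, so a logged analysis would leave the planned scale.

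**What to change.** Delete the Kolmogorov–Smirnov step and fix each outcome's scale before any data are analysed:

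- **Log scale at both visits, reported as geometric-mean ratios:** ALT, AST, ALP, GGT, triglycerides, insulin, HOMA-IR and liver stiffness (kPa).
- **Raw scale, reported as mean differences:** CAP, to match the sample-size calculation, and the remaining outcomes (QUICKI, blood pressure, cholesterol fractions, glucose, anthropometry).
- **Checking:** inspect the residuals of the fitted model graphically, and add a rank-based or bootstrap sensitivity analysis where they look poor. The primary scale should not change as a result.

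The allocation of outcomes to scales is a judgement about their usual skewness, since the article gives no distributions.

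The cost is a few lines of wording. No new data or patients are needed and the stated sample size does not change. The small downside is that readers will see ratios for the log-scale outcomes.

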**Methods:**

Sixty-eight patients with NAFLD will be recruited in this study. After block matching for sex, BMI and age, patients will be randomly assigned to receive 300 g/d probiotic yogurt containing 10^6^ cfu/g of Lactobacillus acidophilus and Bifidobacterium lactis strains or 300 g/d plain yogurt daily for 12 weeks and those in the control group would receive similar amounts of plain yogurts. Weight, height, and waist circumference will be measured at study baseline and after the intervention. Biochemical indicators including plasma glucose, serum insulin, lipid profile, liver markers (ALT, AST and GGT) will be examined at study baseline and at the end of the trial. Insulin resistance and insulin sensitivity will be determined using the HOMA-IR and QUICKI equation. The degree of steatosis and hepatic fibrosis will also be assessed at the beginning and end of the intervention by the same gastroenterologist using elastography with fibroscan.

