### Study design and intervention

A flowchart of the study design is shown Fig. 1. Flow-diagram of study process is shown in Fig. 2. In the first phase of this study, we will screen 300 patients with NAFLD based on the inclusion criteria mentioned above. Then, those who meet the criteria will be included in the study. All participants will be asked to complete and sign the written informed consent. Before the start of intervention, all study participants will be in a 2-week run-in period, during which four 24-h food recalls (two working days and one non-working day) will be used to collect dietary information. In addition, subjects will be requested to record their physical activity for two days (one working day and one weekend day) during this period. Further information about demographic characteristics, past medical history, medication use as well as socioeconomic status (SES) will be collected in this period through the use of a comprehensive questionnaire in a face-to-face interview. Anthropometric indices, blood pressure, liver enzymes, insulin resistance, hepatic steatosis, liver fibrosis and lipid profile will be evaluated at study baseline. Then study participants will be classified into blocks based on age (20–40/ 40–60 years old), sex (male, female) and BMI (25–30/ 30-35 kg/m^2^). Therefore, the size of each block will be 2 people with the same age, sex and BMI. These participants will then be randomly assigned into intervention and non-intervention groups. Randomization will be done by a third person, who is not aware of the study aims and groups. The first person (say A) in a block will be assigned into the intervention group and the second person (say B) in that block will be assigned into the control group. All participants, study personals and laboratory staffs will be blind to the intervention. Participants in the intervention group will consume 300 g/d of probiotic yogurt containing 10^6^ cfu/g of Lactobacillus acidophilus and Bifidobacterium lactis strains for 12 weeks, while participants in the control group will consume 300 g/d of plain yogurt daily (without any added probiotics) for 12 weeks. Yogurt packages will be distributed to participants every two weeks. The appearance, packaging and taste of yogurts will be the same. Quality control of these yogurts in terms of colony forming units of live bacteria and other nutritional values will be evaluated before the study. In order to comply with the ethical requirements in research, all patients will receive a weight loss diet after ending the study. Participants will be asked not to change their routine lifestyle, dietary habits, and medicines throughout the study. All study outcomes will be examined again at the study end. The study was designed according to the Standard Protocol Items: Recommendations for Interventional Trials (SPIRIT) 2013 shown in Fig. 3.

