Despite several strengths of our study protocol including stratified permuted block randomization and double-blind, placebo-controlled design and conducting the study on newly diagnosed NAFLD patients by fibroscan, some limitations must also be taken into account: We will examine the compliance in this study through collecting dietary intake information by questionnaires. Due to limited funding, we are unable to examine gut microbiota and serum trimethylamine N-oxide (TMAO) as a biomarker for assessment of compliance in this study. We also use probiotic strains available in the food market and did not focus on specific strains that might have different effects. Future studies should examine the effect of foods fortified with specific probiotic strains on steatosis and fibrosis in patients with NAFLD. In addition, another concern might be a limited duration of intervention in this study which would be for 12 weeks. Although one might assume this time period too short for our intervention to affect liver fibrosis, other studies have applied almost the same duration for assessing the effect of intervention of fibrosis among patients with NAFLD.

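### The stated model omits the age, sex and BMI factors used to pair patients, so its standard errors may be somewhat too wide

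*Protocol article*

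**What the plan says.** **Design.** The abstract of the protocol article states: "After block matching for sex, BMI and age, patients will be randomly assigned". Under Study design and intervention, participants are "classified into blocks based on age (20–40/ 40–60 years old), sex (male, female) and BMI" (25–30 or 30–35 kg/m²), which makes 2 × 2 × 2 = 8 cells. The same section adds that "the size of each block will be 2 people with the same age, sex and BMI", with one member going to each arm. The Discussion counts "stratified permuted block randomization and double-blind, placebo-controlled design" among the strengths.

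**Analysis.** Under Statistical analysis, "Repeated measure analysis of variance (RM-ANOVA) will be used to examine the effects of probiotic yogurt consumption on outcome variables". The model's terms are time, group and their interaction. One covariate is always in the model: the baseline value of the outcome. Two more, dietary intake and physical activity, enter only if the groups turn out to differ on them during the study. Age, sex, BMI and the pair are not mentioned in that section.

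**The concern.** Pairing makes the arms nearly identical on age, sex and BMI. If these factors are prognostic, the treatment difference then varies less from trial to trial than it would under simple randomisation. A model without the factors does not recognise this: it leaves their contribution in the residual, and the standard error is computed from that residual. The reported standard error then exceeds the true one, confidence intervals are wider than they need be, and the test rejects less often than 5% under the null.

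At stake is efficiency, in a trial planned at 80% power with 28 evaluable patients per arm. The plan does allow adjustment for diet and activity measured after randomisation, yet not for the three baseline variables that define the allocation.

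**Working it through.** **Inputs from the article.** Pairs matched on three two-level factors; 28 evaluable and 34 recruited per arm; 20% drop-out; 5% type I error (taken as two-sided) and 80% power; baseline outcome in the model. The plan gives no figure on this point to reproduce. Its sample size cannot serve as a check either, because no standard deviation is stated. Assignment within a pair is taken as random, and the calculations refer to the baseline-adjusted comparison at week 12.

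**Assumed input.** R is the share of residual variance, after the baseline outcome, that age, sex and BMI explain. The article does not give it, so a range is shown.

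**Step 1: simple formula, complete pairs.** If pairing balances this share fully, then:
- ratio of reported to true SE = 1/√(1−R)
- true type I error = 2[1 − Φ(1.96/√(1−R))]
- power without the factors = Φ((d − 1.96)/√(1−R)), and with them = Φ(d/√(1−R) − 1.96), where d = 1.960 + 0.842 = 2.802 (80% power at R = 0)

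| R | SE ratio | Type I error | Power without | Power with |
|---|---|---|---|---|
| 0 | 1.000 | 5.0% | 80% | 80% |
| 0.05 | 1.026 | 4.4% | 81% | 82% |
| 0.10 | 1.054 | 3.9% | 81% | 84% |
| 0.20 | 1.118 | 2.8% | 83% | 88% |
| 0.30 | 1.195 | 1.9% | 84% | 92% |

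**Step 2: simulation with baseline in the model.** 28 complete pairs, 5,000 runs per setting; the factors are assumed to explain 30% of baseline variance, and the baseline coefficient is 0.6.
- R = 0.20: mean reported SE 0.2143, true SD of the estimate 0.2014, ratio 0.2143/0.2014 = 1.064. Type I error is 3.8%; adding the factors raises power from 79% to 85%.
- R = 0.30: 0.2139/0.1958 = 1.092. Type I error is 3.4%; power rises from 80% to 89%.
- R = 0: power is 78.2% without and 77.6% with the factors, a cost of 0.6 points.

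The ratios are smaller than in Step 1 because, once baseline is in the model, pairing balances only part of what the factors explain.

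**Step 3: how large is R likely to be?** Suppose the factors shift the outcome equally at baseline and at week 12, explaining a share f of outcome variance, with baseline to week-12 correlation r. Then

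R = f(1−r) / [(1−f)(1+r)]

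- r = 0.5: f = 0.10, 0.20, 0.30 gives R = 3.7%, 8.3%, 14.3%.
- r = 0.7: the same f gives R = 2.0%, 4.4%, 7.6%.

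For example, f = 0.20 and r = 0.5 gives (0.20 × 0.5)/(0.80 × 1.5) = 0.083. Baseline has already absorbed most of the factors' effect.

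**Step 4: drop-out.** With independent 20% drop-out, a pair stays complete with probability 0.8 × 0.8 = 0.64, so some of the balance is lost and the test moves back towards 5%. Simulating the Step 3 settings with 20% drop-out gives a reported SE about 1 to 3% too wide, type I error of about 4.4 to 4.8%, and a power change from adjustment of about 0 to 4 points.

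**The case against.** The strongest case against has four parts.

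- **The baseline outcome is already in the model and carries much of what age, sex and BMI would add.** This stands. It is why the upper rows of Step 1 should not be read as the expected loss: they need factors that strongly predict change beyond baseline, and nothing in the article supports that.
- **Validity is not threatened.** This also stands. A reader might infer that omitting the factors biases the result or produces false positives. It does neither: the estimate is unaffected in expectation, and any error in the test is conservative.
- **The benefit of pairing is not thrown away.** A reader might infer that the precision bought by blocking is lost. That is too strong. The estimator keeps its smaller true variance, and power without the factors even rises with R in Step 1 (80% to 84%). Only the reported standard error fails to reflect the gain fully, and if the factors add nothing beyond baseline there is nothing to lose.
- **A journal article may leave the covariate list to a statistical analysis plan.** This stands only in part. The article does not say its list is complete. But it names one fixed and two conditional covariates, so it states a model that leaves out the allocation factors. If a fuller plan includes them, the article's text needs aligning.

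**Conclusion.** The mismatch between design and analysis is real, and its direction is certain wherever the factors predict the outcome beyond baseline: standard errors somewhat too wide and a slightly conservative test. Its size is uncertain because the article gives no share explained.

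The wide range, about 3 to 20% excess in the standard error, rests on R of 5 to 30%, complete pairs and full balance of that share. The narrower range, about 1 to 3%, rests on factors explaining 10 to 30% of outcome variance mostly through baseline, a baseline to week-12 correlation of 0.5 to 0.7, and the planned 20% drop-out. The second set of assumptions is closer to the plan, since it reflects both the baseline adjustment and the expected drop-out. Severity is minor: a cheap improvement, not a threat to the trial's conclusions.

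**What to change.** In Statistical analysis, add age, sex and baseline BMI as prespecified covariates for each outcome, whether or not the groups differ on them. Leave the BMI covariate out where BMI is the outcome, because there it is the same variable as the baseline value. Leave it out for weight too, because of the heavy overlap. The covariates must enter the term that carries the treatment comparison; if that is the time-by-group interaction, they need their own interaction with time.

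This needs no change of model class; whether repeated-measures ANOVA is the best choice is a separate matter.

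All three variables are already collected. The cost is up to 3 degrees of freedom, and under 1 point of power if the factors predict nothing (78.2% to 77.6% in Step 2).

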### Outcomes

The outcomes of the present clinical trial would be assessment of steatosis, fibrosis, serum liver enzyme levels including aspartate aminotransferase (AST), alanine aminotransferase (ALT), alkaline phosphatase (ALP), Gamma-glutamyl transferase (GGT). Systolic (SBP) and diastolic blood pressure (DBP), lipid profiles including high-density lipoprotein cholesterol (HDL-C), low-density lipoprotein cholesterol (LDL-C), total cholesterol (TC), serum triglycerides (TG) fasting blood sugar (FBS), fasting insulin and glucose hemostasis will also be considered. Weight and BMI will also be assessed. All these measurements will be assessed at study baseline and the end of trial.

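### With only two visits, the planned RM-ANOVA uses baseline as both outcome and covariate, so its intervention effect is half the adjusted 12-week difference, and no term is named as the treatment effect

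*Protocol article*

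**What the plan says.** The Outcomes section of the protocol article lists the endpoints and closes: "All these measurements will be assessed at study baseline and the end of trial". The section on hepatic steatosis and fibrosis agrees, with elastography done "by the same gastroenterologist at the beginning and end of the study". No outcome has an intermediate visit.

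The Statistical analysis section chooses repeated-measures ANOVA for the outcome variables, "where we will examine the effects of time, intervention as well as time-group interaction effects". The next sentence reads: "In this analysis, baseline values of outcome variables will be controlled for". It is followed by: "We will also perform post hoc tests after ANOVA analysis to examine the variables between study groups". The section sets significance at 0.05 and names SPSS 26. It does not say which of the three effects measures the benefit of probiotic over plain yogurt, or whether the baseline covariate is centred.

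**The concern.** With two visits, the time factor has two levels and baseline is the first. Controlling for baseline in the same model puts one measurement on both sides of the equation. Three things follow.

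- The term whose name matches the trial question, the intervention effect, averages over both visits. Its baseline half contributes nothing once baseline is a covariate, so the estimate is diluted twofold.
- The intervention and time-by-group terms become one test shown twice, with estimates that differ by a factor of two.
- The time effect is not a randomised comparison, and its meaning depends on how the covariate is coded.

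At stake is the size of the effect that readers and later meta-analyses would take from the trial. A large time effect might also be mistaken for evidence about the yogurt.

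**Working it through.** **Inputs from the protocol article.** Two measurement times (Outcomes; Assessment of hepatic steatosis and fibrosis). Model terms and baseline adjustment (Statistical analysis). 28 patients per arm before drop-out (Participants). For the CAP scale: "CAP results will vary between 100 and 400 dB/m". The article states no figure that this check could reproduce.

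**Assumed, because the article does not give them.** CAP mean 290 and SD 40 dB/m at baseline; treatment effect -20 dB/m; correlation between baseline and week 12 of 0.3, 0.6 or 0.8; two-sided test at 0.05. The factor of one half depends on none of these.

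**Step 1: algebra.** Let Y0 be baseline, Y1 the 12-week value and G the group. Least squares is linear in the response, and regressing Y0 on G and Y0 returns coefficients 0 and 1 with no residual. Hence:

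- ANCOVA: Y1 = a + b·G + c·Y0 + e
- Between-subject part of the RM-ANOVA: (Y0 + Y1)/2 = a/2 + (b/2)·G + ((1 + c)/2)·Y0 + e/2
- Within-subject part: Y1 - Y0 = a + b·G + (c - 1)·Y0 + e

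The intervention coefficient is b/2. Its residual is halved too, so F and p equal those of ANCOVA. The time-by-group coefficient is b with the same residual, so again the same F and p. Further covariates, such as the diet and activity adjustment foreseen in the same section, do not change this. If outcome and baseline are both log-transformed, the halving is on the log scale.

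**Step 2: one simulated data set (28 per arm, correlation 0.6).**

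| Term | Estimate (dB/m) | F | p |
|---|---|---|---|
| ANCOVA, group | -17.597 | 4.040 | 0.0495 |
| RM-ANOVA, time-by-group | -17.597 | 4.040 | 0.0495 |
| RM-ANOVA, intervention | -8.799 | 4.040 | 0.0495 |

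Ratio of intervention to ANCOVA estimate: 8.799/17.597 = 0.500.

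**Step 3: 2,000 simulated trials per setting, true effect -20 dB/m.**

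| Correlation | Mean ANCOVA estimate | Mean intervention estimate | Power (same for both) |
|---|---|---|---|
| 0.3 | -20.03 | -10.01 | 48% |
| 0.6 | -19.89 | -9.95 | 62% |
| 0.8 | -20.06 | -10.03 | 85% |

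**Step 4: the time effect.** With G coded symmetrically around zero and Y0 uncentred, the time test concerns a, the expected change in a patient whose baseline CAP is 0. That is below the stated range. With equal SDs and no mean change in either arm, a = 290 × (1 - correlation): 203, 116 and 58 dB/m for correlations 0.3, 0.6 and 0.8. With Y0 centred at its mean, the coefficient is the mean change pooled over both arms. Rejection rates with no treatment effect and no mean change (2,000 runs each):

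| Correlation | Uncentred | Centred |
|---|---|---|
| 0.3 | 99.8% | 10.7% |
| 0.6 | 94% | 7.6% |
| 0.8 | 66% | 6.5% |

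The centred test still exceeds 5%, because it treats the sample's baseline mean as fixed.

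**Step 5: post hoc tests.** With two groups and one follow-up visit there is a single between-group contrast, already tested by the group term. A between-group post hoc test adds nothing.

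**The case against.** The best defence is that the planned model already contains the right answer. The time-by-group term is listed, and it reproduces ANCOVA in estimate, F and p. The intervention p-value is the ANCOVA p-value as well. This stands, and it limits the point: a reader might infer that the treatment test is invalid or loses power, and the algebra shows that it is not and does not. A large loss of power could be shown for the group main effect in a model without the baseline covariate, but the plan does not propose to rely on that.

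It is also fair that the article nowhere commits to publishing the intervention coefficient as the effect size; it speaks of means with SDs or medians with interquartile ranges. So one cannot say that the published effect will be halved, only that a listed term bearing the obvious name is halved and nothing directs the analyst to the other.

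Two further readings go too far. One might call the time effect meaningless outright. That holds only for an uncentred covariate, and the article is silent on centring, which may be settled elsewhere. One might also take the post hoc tests for before/after tests within each arm. The article says that they compare the study groups, so they are redundant, not misdirected.

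The defence does not remove the central defect. Two visits, a time factor and adjustment for baseline are all stated, and together they define a model in which one listed effect has the wrong size. This is not a detail left to an analysis plan.

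**Conclusion.** The point holds, at moderate weight. As written, the intervention main effect is exactly half the baseline-adjusted 12-week difference estimated by ANCOVA, and half the true effect in expectation. It has the same p-value and power as ANCOVA. The time-by-group term gives the full estimate with that same p-value, so one test appears twice with estimates that differ twofold, and the plan does not name the treatment effect.

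This result is algebraic. It rests only on reading the baseline sentence as a covariate in the same model, which is its natural meaning. The rejection rates for the time effect do rest on the assumed mean, SD and correlations. They show how far the uncentred test can mislead and do not predict this trial. Centred or not, the time effect says nothing about probiotic versus plain yogurt.

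**What to change.** In the Statistical analysis section, replace the RM-ANOVA by one ANCOVA per outcome: the 12-week value on group and baseline value, with the group coefficient and its 95% CI reported as the treatment effect.

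An acceptable alternative is to keep the RM-ANOVA, drop the baseline covariate and name the time-by-group term as the treatment effect. That term compares changes from baseline. With equal SDs and correlation r, its large-sample variance relative to ANCOVA is 2(1 - r)/(1 - r²) = 2/(1 + r): 2/1.3 = 1.54, 2/1.6 = 1.25 and 2/1.8 = 1.11 for the three correlations above. ANCOVA is therefore the better choice.

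Under either option, state that the time effect and post hoc tests are not evidence of efficacy, and drop the redundant between-group post hoc tests. The cost is analysis wording only: no extra data, visits or patients.
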